1. **Conduct a randomized controlled trial assigning worksites in a 2:1 ratio to a multiple-program health intervention or a wait-listed control.** The multiple-program intervention will be a combination of the Human Performance Institute (HPI) intervention and iDiet, a behavioral weight loss program, with randomization to either partial provided food or a gift card for self-selection of food. Within worksites, employees will be eligible to select either the HPI intervention or the behavioral intervention. **Primary outcomes will be quality of life and energy levels (HPI participants and controls) and weight (weight loss intervention participants) at 6-18 months.** Secondary outcomes include cardiometabolic risk factors.
2. *The HPI working hypothesis* is that enrollment in the HPI intervention will result in significant improvements in quality of life (primary outcome) and energy levels compared to controls over 6 months and no significant decrease in quality of life during the subsequent 12-month period in the intervention participants. Exploratory outcomes also tested will include body weight and fat, fasting blood glucose, a lipid panel and systolic and diastolic blood pressure.
3. *The behavioral weight loss program working hypothesis is that* iDiet participants receiving gift card will lose weight over the first 6 months compared to weight listed controls and will lose weight compared to baseline over 18 months. In addition, iDiet participants receiving the ready-prepared foods will lose more weight over 18 months compared to participants receiving gift cards.
4. An exploratory hypothesis is that greater weight loss will be associated with reduced levels of hunger and food cravings and increased satiety.
5. **Background and Rationale**
   1. Background

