2. **Experimental design:** 18-month worksite randomized controlled trial, in which worksites are randomized to receive the multiple intervention wellness programs or the control program. Control participants will participate in outcomes assessments only for the first 6 months, after which they will enroll in the intervention of their choosing. Both arms (HPI and the iDiet) will receive direct training from the coaches who deliver these commercial programs at their respective worksite and/or via a concurrent online session, or at an alternative commutable location that is offsite in the case of the HPI program. A total of 400 participants in the worksites allocated to the intervention, with approximately 20 participants in the HPI arm and 30 in the iDiet arm per worksite is planned to ensure even balance in each of the study arms. If more than 20 individuals are interested in and eligible for the HPI arm or more than 30 are interested in and eligible for the diet arm, participants will be enrolled into the study on a first-come, first-serve basis, including a small upward or downward adjustment in the total number of employees enrolled per site to ensure that the overall targeted number of participants is achieved. All participating individuals, from both the intervention wellness and control programs, can opt-in to either the HPI or the iDiet weight loss program. However, if they choose to participate in the weight loss intervention they will then be randomized into one of two groups: iDiet with food provided or iDiet with a gift card,. The study flow and primary intervention groups are described below:

**
[figure not shown]
**

*^1^The number of controls reflects study design in which sign up for the intervention and distribution of the intervention sites happens before baseline to ensure equivocal disposition*.

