For the HPI intervention in whom those randomized to intervention will be compared primarily with subjects at control sites who elected the HPI intervention prior to workplace randomization, a mixed linear model with worksite nested within the randomization to HPI intervention or control as a random factor will be use to assess the effect of the intervention on change in vitality scale score. Baseline vitality score, weight, ethnicity and gender will be included as covariates.

The diet intervention will compare those receiving the iDiet with a primary outcome of percent change in weight at 6 and 18 months. To assess the effect of diet and food delivery method, a multi-factor model with diet, food and worksite as independent variables will be used, controlling for baseline weight, gender and ethnicity. Interactions between diet and worksite, food and worksite and food and diet will be assessed and included in the final model if significant. Change in weight for the HPI intervention andchange in vitality score for those in the diet intervention will be included as secondary outcomes.

Secondary analyses will include a comparison of the 3 intervention arms (with and without provided food for the iDiet) as well as the combined effect of intervention on change in anthropometric measures including body fat, and also lipids, blood glucose levels and blood pressure using the same models described above adjusting for the appropriate baseline values. Additionally, regression models will be used to assess the effect of different adherence metrics, activity levels, appetite regulation (hunger and food cravings) and measures of wellbeing on outcome measurements both within and between intervention groups for each arm of the study. In addition, predictors of changes in cardiometabolic parameters will be examined. Prior to enrollment of subjects, a formal data analysis plan will be prepared and submitted as part of clinical trial registration.

1. **Worksite Characteristics**

A convenient sample of worksites in the Greater Boston area, consisting of worksites which have previously expressed interest, and respond to the recruitment letters will be invited to participate in the Worksite Wellness Study. The first twelve eligible worksites with a higher employee interest in worksite wellness will then be invited to enroll in the study.

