**Table 1: Overview of Assessments and Assessment Schedule (in weeks):**

|  | **Intervention Worksites – HPI and iDiet Groups*** | **Control Worksites – Future HPI, and iDiet Groups*** |
| --- | --- | --- |
| **Measurements** |  |  |
| **Weight at site** | **0, 3, 6, 9, 12, 15, 18** | **0, 3, 6** |
| **Blood Pressure, Fasting lipid panel and Glucose** | **0, 6, 12, 18** | **0, 6** |
| **Waist and Hip Circumference** | **0, 6, 12, 18** | **0, 6** |
| **% Body fat** | **0, 3, 6, 12, 18** | **0, 3, 6** |

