Participants will receive up to $75 over the course of the study, for completing the assessments outlined at each time point (Table 1). Participants will receive this amount as $25 for doing all 6 month testing, $25 for doing all of month 12 testing, and $25 for doing all of month 18 testing. These amounts will be prorated and given to participants based on completion of testing at each time point and if participants withdraw, or are withdrawn from the study for any reason. If institutional policy dictates that employees are not allowed to receive such stipends then such policies will override the provision of stipends as stipulated for each time point.

For diet intervention participants randomized to the voucher group, vouchers of $63 will be given at baseline and weeks 4, 8, 12, and 16, 20 the time of food distribution, for a total of $378 in gift card vouchers.

1. **Payment for research-related injury:** Subjects will be encouraged to see their primary care physician, however no monetary compensation for injury will be offered.
2. **Outcomes**

The primary outcomes are a change in measured weight from baseline to 18 months in iDiet participants, and a statistically significant improvement in energy status for HPI participants and baseline to 6 months in comparisons with the controls. Additional outcomes include: cardiometabolic risk factors, quality of life, employee productivity, purpose in life, measured dietary intake and cravings, satiation and satisfaction of food provisions, as well as changes in physical activity. Further outcomes include changes in weight, blood pressure employee energy and productivity in non-participating employees at the intervention worksites. Differences in overall mean values between the intervention participants and controls, as well as overall mean values between interventions will be compared using *t*-tests and proportions will be compared using *χ*2 analyses.

1. **Tissue banking considerations:** There will be no tissue samples taken as part of this study and no tissue banking is planned or anticipated.

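### The 18-month hypothesis for gift-card iDiet participants is an uncontrolled comparison with their own baseline, so it cannot show what iDiet itself did to weight

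*Protocol*

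**What the plan says.** Under Aim and Hypotheses, the protocol makes three statements about weight in iDiet participants:

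- Gift-card participants "will lose weight over the first 6 months compared to weight listed controls". The comparator is the randomised wait-list.
- The same participants "will lose weight compared to baseline over 18 months". The comparator is their own starting weight.
- "iDiet participants receiving the ready-prepared foods will lose more weight over 18 months compared to participants receiving gift cards". The comparator is the other randomised iDiet group.

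The Experimental design section explains why the comparator changes after month 6: "Control participants will participate in outcomes assessments only for the first 6 months, after which they will enroll in the intervention of their choosing". Table 1 agrees. It schedules weights up to time point 18 at intervention sites and stops at 6 at control sites.

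The Outcomes section says: "The primary outcomes are a change in measured weight from baseline to 18 months in iDiet participants". It names no comparator for that outcome, whereas the HPI outcome in the same sentence is set against the controls.

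The analysis paragraph under Sample size and statistical analyses says: "The diet intervention will compare those receiving the iDiet with a primary outcome of percent change in weight at 6 and 18 months". The preceding paragraph gives HPI a mixed model with worksite as a random factor, comparing intervention participants with control-site participants who chose HPI before randomisation. No matching model is given for iDiet against control.

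**The concern.** A comparison with baseline has no term for weight change that would have happened without the programme. These participants chose a weight-loss arm, had to have a BMI of at least 25 at screening, are weighed repeatedly for the study and, in this group, receive $378 in gift cards. Any of these could move weight, and so could ordinary gain or regain over 18 months. The comparison with baseline reports the sum of all of it.

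This matters because the protocol presents lasting change as central to its purpose, and the 18-month clause is part of the working hypothesis. The sample size section applies a two-sided 0.05 threshold to all testing. A significant 18-month loss could therefore be read as lasting iDiet effectiveness, although the only randomised evidence on iDiet versus no programme ends at month 6.

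**Working it through.** **Which comparisons are randomised**

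| Time | Comparison | Randomised? | Can it show that iDiet works? |
|---|---|---|---|
| 6 months | Gift card vs wait-list | Yes, by worksite | Yes |
| 18 months | Food vs gift card | Yes, within iDiet | No, both groups receive iDiet |
| 18 months | Gift card vs own baseline | No | No |

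HPI participants are also followed to month 18, but they chose their programme and are not a randomised control for iDiet.

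**How much background change could matter (illustration only)**

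The protocol gives no sample size or power for the 18-month comparison with baseline, so there is no stated figure to reproduce. It also gives no SD for weight change and no expected change in untreated participants. The SD is back-solved and the background change is assumed.

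1. *SD.* The sample size section gives 240 iDiet participants, half in each group, and at least 80% power for a 2.4% difference. Treating power as exactly 80%:
   SD = 2.4 / [(1.960 + 0.842) × √(2/120)] = 6.64%.

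2. *Ignoring worksite.* With 120 gift-card participants and no dropout:
   SE = 6.64/√120 = 0.606%. With 119 df the critical t is 1.980, so a mean loss of 1.980 × 0.606 = 1.20% is significant.

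3. *Allowing for worksite.* With 8 sites of 15 gift-card participants and 7 df (critical t 2.365):
   SE = SD × √{[ICC + (1 − ICC)/15]/8}.
   - ICC 0.01: SE = 0.647%, threshold 1.53%.
   - ICC 0.05: SE = 0.790%, threshold 1.87%.

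4. *Chance of a significant two-sided result if iDiet has no effect* (noncentral t with noncentrality = background loss / SE):

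| Assumed background loss | Ignoring worksite | ICC 0.01 | ICC 0.05 |
|---|---|---|---|
| 0 | 5% | 5% | 5% |
| 0.5% | 13% | 10% | 9% |
| 1.0% | 37% | 27% | 20% |
| 1.5% | 69% | 52% | 38% |

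5. *Sensitivity to SD at 1% background loss.* Ignoring worksite, the chance is 58% at SD 5% and 27% at SD 8%. At ICC 0.05 it is 31% and 15%.

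6. *The other direction.* Suppose iDiet truly causes a 2% loss. Ignoring worksite, the test against zero is significant 91% of the time with no background change. If untreated weight would have risen by 1%, the net loss is 2 − 1 = 1%, and the figure falls to 37%.

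**The case against.** The strongest reply is that the plan hides nothing. The hypothesis names baseline as its comparator and places that clause after a controlled 6-month claim. It can be read as a controlled effect followed by durability, and HPI has the same structure. The protocol calls the later phase structured maintenance. A wait-list design that releases its controls at month 6 cannot have an untreated group at month 18. Both randomised contrasts are already stated. All of this stands, and it limits the point to how one clause and one outcome are labelled and used.

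Several stronger readings do not hold:

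- A reader might infer from the Outcomes section that a one-sample test is the planned primary analysis. That section defines an outcome variable and goes on to mention comparisons between intervention and control participants and between interventions. No one-sample test is written anywhere; the one above is an illustration.
- A reader might assume that background change favours iDiet. The documents give no expected change in untreated participants, and the background section describes work environments that promote obesity. Bias could run either way.
- A reader might treat the figures that ignore worksite as the size of the problem. They fall by roughly a third to a half at 0.5% to 1.5% background loss once an ICC of 0.05 is allowed for.
- A reader might take the 3% improvement in diet in the sample size section as the expected gift-card versus control effect and compute 6-month power from it. That figure belongs to an interaction power statement and does not describe this contrast.

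The durability reading does not fully answer the point. The clause is part of the working hypothesis alongside the controlled claims, and nothing labels it as descriptive.

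**Conclusion.** The concern holds in limited form. The 18-month claim for gift-card participants is uncontrolled and cannot separate an iDiet effect from other weight change, and the related primary outcome has no stated comparator. The 6-month hypothesis against controls and the 18-month food versus gift-card hypothesis are unaffected, so the documents do not support saying that iDiet lacks any controlled evaluation.

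With no iDiet effect and a 1% background loss, a test against zero would be significant about 37% of the time ignoring worksite, or 20% to 27% at ICC 0.05 to 0.01. This rests on an assumed background change, assumed ICCs, an SD back-solved from a power statement that names no time point, and 120 participants with no dropout over 18 months. The figures show that modest background change is enough to matter; they do not predict this trial's result. The conclusion about the comparator needs none of these assumptions.

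**What to change.** 1. **Aim and Hypotheses.** Report the gift-card group's 18-month change as a descriptive mean with 95% confidence interval, labelled as uncontrolled maintenance, and not as a test of effectiveness. Rest the iDiet effectiveness claim on the 6-month contrast between gift-card participants and control-site participants who chose iDiet before randomisation.
2. **Sample size and statistical analyses.** Add that 6-month contrast explicitly, with worksite as a random factor, as is already done for HPI. Rewording the hypothesis alone is not enough, because the diet paragraph as written compares only iDiet recipients.
3. **Outcomes.** State the 18-month iDiet primary comparison as the randomised food versus gift-card difference.

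No new participants, visits or measurements are needed. The cost is text changes in three sections, one added model, and the loss of an 18-month p-value against baseline.

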- **Yevo Foods:** Participants will be given commercial dried food products from Yevo Intl., which are designed to help with weight control and health. Of the participants selecting the iDiet, half the group will be randomized to receive Yevo foods. Participants will be supplied with these foods monthly at the worksite for the first six months (equivalent to 2 meals/day during the first 12 weeks, and 1 meal/day for the following 12 weeks). No meals will be provided after this period, however weight maintenance in participants randomized to receive the meal will be examined for over the 18 month study duration. Participants will be asked to communicate directly with research staff for questions about Yevo foods and food vouchers, not with iDiet staff.
- **Gift Cards:** The remaining half of the iDiet participants will be randomized to receive gift cards monthly for the first 6 months, for a total of $378 and will be encouraged to purchase foods at their local grocery store.

1. **Sample size and statistical analyses**

Primary randomization is at the level of the worksites using a 2 to 1 allocation in favor of intervention; 8 worksites will receive the intervention package consisting of the 3 wellness programs and 4 worksites will be randomized as wait-listed controls.

We will enroll up to 700 individuals among 12 worksites with the goal of having 600 complete baseline assessments and get randomized to their intervention. 400 will receive one of the two intervention arms at the intervention sites, while 200 participants will be in the control sites and will participate in outcome assessments only for a six month period.

Primary outcomes measured in this study will be the change in (energy levels) vitality score as measured by the SF-36 questionnaire and change in weight from baseline to 6, 12 and 18 months. Vitality will be the primary outcome in participants in the HPI arm of the study, while weight will be the primary outcome in participants in the behavioral weight loss arm of the study.

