The increase in vitality score in the intervention worksites compared to controls is expected to be 9 points at both time points compared to the control. Since randomization is at the worksite level, the total variance includes both the within worksite and between worksite variance. Based on a within worksite standard deviation of 15 and 20 people per worksite and a between worksite standard deviation of at most 3.4, 12 worksites with a 2:1 worksite allocation in favor of treatment are needed to have 80% power to detect an expected increase in vitality score of 9 points.

For the participants electing to participate in the behavioral weight loss program, randomization to either with provided Yevo foods or a gift card such that one half of the participants are in one group and the other half will be assigned to the remaining arm.. Assuming worksite is a fixed variable, 8 worksites with 30 subjects each (240 total subjects) is at least 80% powered to detect a 2.4% difference in weight loss with provided food compared to gift cards assuming no diet by food interaction. If there is a significant food by diet interaction, the study will have an 80% power to detect an interaction that is a 4.5% difference in weight change with provided food for iDiet and 3% improvement in diet.

Data analyses will be performed using the latest version of SAS for Windows, currently 9.4 (Cary, NC: SAS Institute Inc.). All testing will be two-sided and results will be judged statistically significant if the observed significance level (P value) is <0.05. Data will be examined graphically and numerically for outliers and other aberrations that might lead to misleading results. Data may be transformed prior to formal analysis if necessary to fit the assumptions for the statistical model to be employed. Both studies (HPI intervention and the iDiet intervention) will be analyzed according to Intention-To-Treat principles to best reflect what happens when individuals start one of the interventions. If necessary, missing data will be estimated using multiple imputations using the MI Procedure of SAS for Windows.

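### The protocol states the primary outcome, scale and time point inconsistently under three headings, although comparison with the wait-list control is possible only to 6 months

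*Protocol*

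**What the plan says.** **HPI programme**
- Aim and Hypotheses, first objective: "Primary outcomes will be quality of life and energy levels (HPI participants and controls) and weight (weight loss intervention participants) at 6-18 months".
- Aim and Hypotheses, HPI hypothesis: enrolment will "result in significant improvements in quality of life (primary outcome) and energy levels compared to controls over 6 months". Maintenance over the following 12 months is then assessed in intervention participants only.
- Sample size and statistical analyses, outcome definition: "change in (energy levels) vitality score as measured by the SF-36 questionnaire and change in weight from baseline to 6, 12 and 18 months", with vitality assigned to HPI and weight to the weight-loss arm.
- Same section, power paragraph: the vitality gain is "expected to be 9 points at both time points compared to the control". The two times are not named.
- Outcomes: energy status from baseline to 6 months against controls is primary, and quality of life is listed among the additional outcomes.

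**iDiet programme**
- Aim and Hypotheses: gift-card iDiet against wait-list controls over 6 months, iDiet against baseline over 18 months, and provided food against gift card over 18 months.
- Sample size and statistical analyses, outcome definition: change in weight at 6, 12 and 18 months.
- Same section, analysis paragraph: "a primary outcome of percent change in weight at 6 and 18 months".
- Outcomes: "The primary outcomes are a change in measured weight from baseline to 18 months in iDiet participants".

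**Control follow-up.** Control-site participants "will participate in outcome assessments only for a six month period". Experimental design adds that they then enrol in a programme of their choice. Tables 1 and 2 list control weight and SF-36 at 0, 3 and 6 only.

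**Test level.** All tests are two-sided and judged at P<0.05.

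**The concern.** These statements cannot all be followed. Quality of life cannot be both the HPI primary outcome and an additional outcome. Vitality cannot be primary at three times, at two unnamed times and at one time. For iDiet, the set of primary times differs in each statement, and only one names percent change as the scale.

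Some of these choices would also have no control. A reader who takes the 12- and 18-month vitality times as primary finds no concurrent control SF-36 data there.

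As written, a result on any of several outcomes, scales or times could be reported as the primary result and traced to some sentence in the protocol. That changes what the trial can claim to have confirmed, and it separates the stated power from the test that it was calculated for.

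**Working it through.** **1. Which primary times have a control.** Tables 1 and 2 are headed in weeks, but Study Procedures gives the 6, 12 and 18 visits in months, so I read them as months.

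| Comparison | 6 months | 12 months | 18 months |
|---|---|---|---|
| HPI vs wait-list, vitality | yes | no | no |
| iDiet vs wait-list, weight | yes | no | no |
| Food vs gift card, weight | yes | yes | yes |

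The Anthropometry text mentions weights at 12 and 18 months in all subjects. Even if control-site participants were weighed then, they would already have started an intervention, so those weights would not be control data.

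**2. The plan's own vitality power.** Inputs from the sample-size section: within-site SD 15, 20 people per site, between-site SD 3.4, 8 versus 4 sites, difference 9, two-sided 5%.
- Variance of a site mean: 3.4² + 15²/20 = 11.56 + 11.25 = 22.81.
- SE of the difference: √[22.81 × (1/8 + 1/4)] = √8.554 = 2.925.
- Non-centrality: 9 / 2.925 = 3.077.
- Power from the non-central t with 12 − 2 = 10 df: **79.2%**, against 80% stated. The normal approximation gives 86.8%.

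The stated figure is therefore reproduced, for a single test at 5%.

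**3. Power if the 5% were split over several vitality tests** (same inputs, t with 10 df):

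| Tests | Level each | Power for each |
|---|---|---|
| 1 | 0.05 | 79.2% |
| 2 | 0.025 | 67.1% |
| 3 | 0.0167 | 59.5% |

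**4. False-positive chance if any one time could count as primary at 5%, within one programme.**
- Independent tests: 1 − 0.95² = 9.75% for two times; 1 − 0.95³ = 14.3% for three.
- Equally correlated normal test statistics, 1,000,000 simulated draws. The documents give no correlation, so the values are assumed:

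| Assumed correlation | Two times | Three times |
|---|---|---|
| 0.5 | 9.1% | 12.5% |
| 0.7 | 8.4% | 10.9% |
| 0.8 | 7.8% | 9.8% |
| 0.9 | 7.1% | 8.4% |

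Repeated measurements on the same people are correlated, so 14.3% is an upper reference. The three-time case fits food versus gift card most directly, because that comparison is randomised at all three times. For HPI it would arise only if uncontrolled 12- and 18-month changes were counted as primary results.

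**The case against.** **The analysis plan may settle the testing order.** The protocol promises a formal data analysis plan before enrolment, and that plan is not at hand. A reader might infer that success can be claimed on several 5% tests because no hierarchy exists. The documents do not support that: a hierarchy may be set elsewhere, and its absence from the protocol is not the finding. The conflict remains, because no analysis plan can agree with all the protocol's statements at once.

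**Control comparisons are mostly confined to 6 months.** The aims and the Outcomes section both tie the HPI control comparison to 6 months, and the aims do the same for iDiet against control. The definition listing 6, 12 and 18 months does not say that the later times are compared with control. A reader might infer that two of the three primary times have no control at all. That is too strong, since food versus gift card keeps its comparator to 18 months. The two unnamed vitality times could even be months 3 and 6, the only post-baseline control SF-36 visits, although month 3 is nowhere named as a primary time. The phrase is ambiguous; it does not prove that an impossible test was planned.

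**HPI and iDiet are separate studies.** A reader might count two outcomes at three times as six tests, giving 1 − 0.95⁶ = 26.5%. That pools two self-selected populations that each have their own primary outcome, and it counts vitality times without a control. One 5% test per programme is defensible, so only the within-programme figures are used here.

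**Some differences are terminology.** The protocol equates energy levels with SF-36 vitality, so energy status can be the same outcome. Change in measured weight need not mean kilograms, and percent matches the power statement. Both points stand. They do not resolve the quality-of-life conflict or the differing times.

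**Conclusion.** The point holds as an internal contradiction. The primary outcome is stated inconsistently under three headings: Aim and Hypotheses, Sample size and statistical analyses, and Outcomes. For HPI the outcome and time conflict. For iDiet the times conflict, and the scale is stated only once. Vitality and iDiet against wait-list control can be tested to 6 months only.

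If any of three times in one programme could serve as primary, the false-positive chance is about 8% to 12.5% at assumed correlations of 0.9 to 0.5, and 14.3% under independence, instead of 5%. These figures are conditional on that use. The 80% vitality power is sound for one test at 5%, and 6 months is the only named primary time with a control. This should be corrected, because it decides which results count as confirmatory.

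**What to change.** Use one identical statement of outcome, scale, time and comparator per programme in the aims, the outcome definition, the power paragraph, the analysis paragraphs and the Outcomes section.

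- **HPI:** change in SF-36 vitality from baseline to 6 months, against control-site participants who elected HPI before worksite randomisation. In the power paragraph, replace the two unnamed times with 6 months. Make quality of life secondary, and make 12- and 18-month vitality secondary and within-arm only.
- **iDiet:** name one primary comparison, scale and time. Percent weight change, provided food versus gift card, at 18 months is consistent with the aims, the power and analysis paragraphs and the Outcomes section. This is a proposal: the power statement for that comparison names no time point, and the sponsor should add one.
- **Other iDiet results:** label the remaining weight times and gift-card iDiet versus control at 6 months as secondary, or place them in an order that the sponsor prespecifies.

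The cost is protocol wording and alignment of the registration. The downside is that fewer results can be called primary.
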